#### Bradycardia/tachycardia

- Bradycardia is defined as a heart rate < 50 bpm, except in individuals with a known baseline heart rate below this threshold and high exertional capacity. Tachycardia is defined as a heart rate > 150 bpm.
- Three consecutive heart rate measurements will be taken 5 minutes apart, along with an ECG reading. If the heart rate does not start increasing (for bradycardia) or decreasing (for tachycardia) after three measurements, the research visit will be discontinued.
- If the heart rate is < 50 bpm for three consecutive measurements and the participant shows signs of poor perfusion (e.g., altered mental status, signs of shock, chest pain), atropine 0.4mg will be administered AND call 911.
- If the heart rate is > 150 bpm and the participant is stable but the rhythm is irregular on ECG, call 911.
- Determine if a pulse is present:
  - If no pulse (e.g., ventricular tachycardia, ventricular fibrillation, or pulseless electrical activity): Immediately initiate basic life support (BLS) and advanced life support (ACLS) protocol for cardiac arrest (see below).
  - If a pulse is present: Provide oxygen if hypoxic AND call 911 AND insert IV if time while awaiting emergency response.

- Note: We do not have the ability to perform synchronized cardioversion or administer antiarrhythmics.

#### Cardiac Arrest

- Research visit will be discontinued.
- The clinical research coordinator will call 911, while the study clinician initiates BLS and ACLS protocols. Specifically, CPR will be administered and AED pads placed by an ACLS/BLS certified provider. Shock will be administered by an ACLS/BLS certified individual according to the directions of the AED (located in the scan room within CNI) with continued CPR and concurrent administration of epinephrine 1 mg IV every 3-5 minutes until the ambulance arrives.
  - Epinephrine will need to be diluted with 9 mL of normal saline to create a 1:10,000 (1mg/10mL) concentration.
    - Start with a 10 mL normal saline flush
    - Waste 1 mL from the flush
    - Draw 1 mL of epinephrine (1mg/mL) into the flush and mix. Remove any air bubbles prior to IV administration.
    - DO NOT mix ahead of time

#### Allergic Reaction

- Research visit will be discontinued.
- In case of mild to moderate allergic reaction, diphenhydramine 25mg PO will be administered by the clinician. Mild symptoms could include though are not limited to hives/rashes and itching.
- If symptoms are severe, including but not limited to swelling of the throat/and or tongue, difficulty breathing or swallowing, and/or drop in blood pressure, administer EpiPen 0.3mg Auto-injector, preferably by the clinician. 911 should be called simultaneously by a clinical research coordinator.
- For oxygen saturation <85%, a nasal cannula will be placed by the clinician until saturation reaches at least 90%.

#### Nausea

If the subject reports that they are feeling nauseous, the following procedure will be followed:

- The clinician will ask the subject if their nausea is mild, moderate, or severe.
- If the subject reports that their nausea is Moderate or Severe, the study clinician will administer 4mg of Zofran, sublingual.
- If the subject reports that their nausea persists and that it is severe, 911 will be called.
- All Other Emergencies
  - 911 will be called. The Palo Alto Fire Department response time from the time of the call to the scanning facility is 6 minutes or less, 90% of the time.

## **2.8 Relevant concomitant care permitted or prohibited during the trial**

Research coordinators will record all concomitant medications participants use regularly or intermittently beginning at the in-person screening visit and at each consecutive visit throughout the study. All psychoactive medications, herbal supplements, non-prescription medications, and prescription medications must be reviewed by the research team prior to a participant being enrolled in the study. Emergency medications including nitroglycerin tablets, epinephrine auto-injector, diphenhydramine capsules, atropine sulfate, epinephrine ampoules, diphenhydramine vials, and sublingual Zofran will be kept onsite for administration by the study clinician in the case of emergency or participant need.

## **2.9 Eligibility criteria**

Inclusion Criteria:

- Ages 18-55
- All genders and ethno-racial categories
- At least 2+ prior uses of MDMA when aged 18 years or older and have reported no serious adverse reactions from MDMA or ecstasy
- Able to swallow capsules
- Able to receive an MRI
- Able to comply with study procedures
- Able and willing to enroll and provide written informed consent

Exclusion Criteria:

- Current mood or anxiety disorder
- Current or past eating, bipolar, or psychotic disorder
- Current substance or alcohol use disorder
- Current suicide risk as assessed by psychiatric interview and clinical judgement of the investigator
- Schizophrenia in a first degree relative
- Allergy or hypersensitivity to MDMA
- Have used Ecstasy/MDMA within 6 months of the first study dose; or have previously participated in a MAPS-sponsored MDMA clinical trial
- Concurrent use of any medication or substance that might increase the risk of participation and/or interact with MDMA
- Current use of any psychotropic medication (a wash-out period of 5 half-lives will be required prior to drug visits followed by a 1-week stabilization period, if the participant reports recently discontinuing a psychotropic medication)

- Unable or unwilling to agree to refrain from using any psychoactive substances, supplements, and nonprescription medications starting 1-week prior to study start and for duration of study
- Unable or unwilling to refrain from using caffeine for 12 hours before and 10 hours after drug administration
- Direct physical access to or routine handling of addicting drugs in the regular course of work duties
- Current use of any opioids, including codeine, hydrocodone, and morphine
- Positive test on urine drug screen for illicit and/or drugs of abuse at screening and prior to study drug administration
- Body Mass Index (BMI) outside of healthy range (18-30)
- Pregnant or nursing
- Renal/hepatic impairment (assessed via laboratory tests during initial screening appointment)
- Uncontrolled hypertension as defined by a systolic blood pressure  $\geq 140$  mmHg or diastolic blood pressure  $\geq 90$  mmHg on two of three measurements at least 15 minutes apart at initial screening appointment
- Heart rate  $< 50$  bpm or  $> 150$  bpm assessed at initial screening visit
- Current chronic congestive heart failure, tachyarrhythmias, myocardial ischemia (assessed via Electrocardiogram (ECG) at initial screening appointment)
- Marked Baseline prolongation of QT/QTc interval e.g., repeated demonstration of a QTc interval  $> 450$  milliseconds (ms) in males and  $> 460$  ms in females. For transgender or non-binary participants, QTc interval will be evaluated based on sex assigned at birth, unless the participant has been on hormonal treatment for 5 or more years
- Current or history of significant (controlled or uncontrolled) hematological, endocrine, cerebrovascular, cardiovascular, coronary, pulmonary, renal, gastrointestinal, immunocompromising, or neurological disease, including seizure disorder, or any other medical disorder judged by the investigator to significantly increase the risk of MDMA administration (participants with hypothyroidism who are on adequate and stable thyroid replacement will not be excluded).
- History of additional risk factors for Torsade de pointes (e.g., heart failure, hypokalemia, family history of Long QT Syndrome)
- History of hyponatremia or hyperthermia
- Inability to speak, read or understand English at a 5th grade level or severe hearing impairment
- Plan to move out of the area during the study period
- An exclusionary metal device as determined by the discretion of the Clinical Investigator.

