## **2.5 Interventions**

### *2.5.1 Intervention description*

After baseline visit, each participant will receive placebo, 80mg MDMA HCl, and 120mg MDMA HCl in a randomized order. Given the within-subjects design of the study, each participant will receive all three of the specified doses across the duration of the trial. Drug visits will be scheduled 10-14 days apart to avoid drug carry-over effects. Participants will arrive fasted for drug visits in the morning to reduce the risk of emesis. They will complete a urine drug screen and pregnancy test (if applicable) and have their baseline vitals recorded at the Stanford Center for Cognitive and Neurobiological Imaging, where they will be met by the study clinician. Participants will be instructed to orally ingest pills with water or an electrolyte solution. For safety reasons, pulse, blood pressure, temperature, and oxygen saturation will be monitored and recorded every 30 minutes throughout the drug visit. The total visit time for drug visits will be 6-8 hours.

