#### Severe Hypertension

*Severely elevated blood pressure* will be considered a systolic blood pressure > 200 or a diastolic blood pressure > 115 mmHg.

- Attempt non-pharmacologic interventions, such as dimming the lights and creating a relaxing environment.
- Take three consecutive blood pressure measurements, 5 minutes apart, with ECG monitoring. If blood pressure does not decrease after three measurements, the research visit will be discontinued.
- If there is no decrease after the 3rd measurement OR the participant reports chest pain at any time in conjunction with high blood pressure OR has ECG changes suggestive of ischemia in conjunction with high blood pressure, the study clinician will administer NitroStat 0.4 mg sublingual tablet AND call 911.
- If the participant experiences symptoms such as blurred vision, headache, or chest pain in conjunction with severely elevated blood pressure, 911 will be called immediately.

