## **2.10 Recruitment and Study Cohort**

Healthy volunteers who report  $\geq 2$  uses of MDMA when they were 18 years or older, recruited to attain 4 sessions of data during functional brain imaging. A total of 40 participants will be recruited, equal

numbers of males and females will be recruited. Participants will be recruited through Facebook Ads using IRB-approved material. Individuals who express interest in the study will be directed to an online screening survey in REDCap. Completed screening surveys will be reviewed by research coordinators trained on the study protocol. Surveys will collect information about demographics, psychiatric diagnoses, substance use, and MRI compatibility. Individuals that are eligible by the criteria included in the screening survey will be contacted by a research coordinator to schedule a phone call. On this phone call, research coordinators will give the individuals additional information about the study and collect additional demographic information. Eligible individuals at this point will be consented by a research coordinator and will schedule an in-person screening visit at a research clinic to fully determine eligibility. The following procedures and assessments will be performed at the screening visit: ECG, physical examination, blood draw, vital signs, weight, urine drug test, pregnancy test (if applicable), Hamilton Anxiety Rating Scale (HAM-A), Hamilton Depression Rating Scale (HAM-D), the Mini International Neuropsychiatric Interview (MINI).

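### The upper heart-rate limit for entry (> 150 bpm) is the same number as the drug-visit tachycardia limit, so it leaves as little as 0 bpm of headroom

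*Protocol*

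**What the plan says.** **Entry.** Section 2.9 excludes a heart rate below 50 or above 150 "bpm assessed at initial screening visit". It does not say that the rate is taken at rest or repeated. For blood pressure, the same section excludes a systolic value of 140 mmHg or more, or a diastolic value of 90 mmHg or more, "on two of three measurements at least 15 minutes apart at initial screening appointment".

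**Drug visit.** Under Bradycardia/tachycardia, section 2.7 states: "Tachycardia is defined as a heart rate > 150 bpm". The response begins as follows: "Three consecutive heart rate measurements will be taken 5 minutes apart, along with an ECG reading". The visit is stopped if the rate does not begin to fall, and 911 is called if the rhythm is irregular. Under Severe Hypertension, severely elevated blood pressure "will be considered a systolic blood pressure > 200 or a diastolic blood pressure > 115 mmHg".

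**Other screens.** Section 2.9 excludes tachyarrhythmias found on the screening ECG. It also excludes significant cardiovascular and endocrine disease and "any other medical disorder judged by the investigator to significantly increase the risk of MDMA administration". Section 2.10 lists among the screening procedures "ECG, physical examination, blood draw, vital signs, weight, urine drug test". On drug visits, section 2.5.1 has participants "have their baseline vitals recorded at the Stanford Center for Cognitive and Neurobiological Imaging" but gives no heart-rate value at which the dose is withheld.

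**The concern.** An entry limit on a vital sign that the study watches under drug should leave room for the sign to rise. This one leaves none. It removes only people who would already meet the drug-visit definition of tachycardia without having taken anything, so it adds no safety margin of its own. Volunteers with an undosed rate of 101 to 150 bpm pass the numeric rule and depend on judgement without a number before they receive 80 mg or 120 mg of MDMA.

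Two other parts of section 2.7 add weight. The site states that it cannot cardiovert or give antiarrhythmic drugs, so selection at entry matters more. In a myocardial infarction, nitroglycerin is withheld when the heart rate exceeds 100 bpm. A volunteer admitted above 100 bpm whose rate did not fall would be outside that treatment window at their own baseline.

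What is at stake is participant safety. No endpoint, power figure or error rate depends on it.

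**Working it through.** All limits are taken from protocol sections 2.7 and 2.9. Headroom is the emergency limit minus the entry limit.

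| Vital sign | Excluded at entry (2.9) | Emergency limit (2.7) | Headroom |
|---|---|---|---|
| Heart rate, upper | > 150 bpm | > 150 bpm | 150 − 150 = 0 bpm |
| Systolic pressure | ≥ 140 mmHg | > 200 mmHg | 200 − 140 = 60 mmHg |
| Diastolic pressure | ≥ 90 mmHg | > 115 mmHg | 115 − 90 = 25 mmHg |

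1. Both heart-rate rules are strict inequalities at 150. A rate of exactly 150 bpm passes entry, and any rise above it meets the tachycardia definition.
2. For a screening rate h that the criterion admits, headroom is 150 − h. It is 49 bpm at h = 101 and falls to 0 at h = 150. Starting this range just above 100 bpm is an assumption. Within the protocol, 100 bpm appears as a heart-rate limit only in the nitroglycerin rule.
3. No other criterion closes the range with a number. The tachyarrhythmia exclusion gives no rate and does not say whether a fast sinus rhythm counts. The disease exclusion concerns medical disorders, which a fast sinus rate alone need not be. The pre-dose vital signs are recorded without a stated heart-rate limit.
4. Headroom under alternative entry limits (assumed range):
   - 100 bpm: 150 − 100 = 50 bpm
   - 110 bpm: 150 − 110 = 40 bpm
   - 120 bpm: 150 − 120 = 30 bpm

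The lower limit is also shared: 50 bpm at entry and on drug. The drug-visit rule exempts people with a known baseline below 50 bpm, although a screening rate below 50 bpm already excludes. This suggests that the emergency limits were reused for screening, but the protocol does not say so.

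**The case against.** The strongest reply is that the number hardly matters, because so much else stands between a volunteer with a fast heart rate and the drug. Besides the ECG, physical examination and disease exclusions, section 2.9 removes common causes of a fast rate: current anxiety disorder, substance or alcohol use disorder, psychotropic medication, interacting drugs, and a positive urine screen at screening or before dosing. Entrants must have used MDMA at least twice without a serious reaction. A clinician meets the participant at each drug visit, and pulse is recorded every 30 minutes. A clinician could also treat persistent sinus tachycardia as a tachyarrhythmia. This stands as a reason to expect few affected people. It does not supply a number, and an explicit limit of 150 bpm beside these criteria may suggest to staff that lower rates are acceptable.

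Three narrower points also stand:

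- Exceeding 150 bpm on drug first triggers repeat readings and an ECG, so it is not by itself an automatic emergency call.
- Section 2.5.1 sets no pre-dose limit for any vital sign, so that gap is not peculiar to heart rate.
- The protocol gives no size for MDMA's effect on heart rate, so it cannot show how much headroom is needed. The blood-pressure gaps show that the protocol leaves room elsewhere. They do not determine the right heart-rate limit.

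None of these alters the match between the two limits or the absence of a lower heart-rate number for entry.

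**Conclusion.** The concern holds. The upper screening limit and the drug-visit tachycardia limit are both > 150 bpm, so the numeric criterion leaves as little as 0 bpm, against 60 mmHg systolic and 25 mmHg diastolic for blood pressure. The match of the numbers is certain. The practical consequence is less so: the protocol does not say how many volunteers would screen at 101 to 150 bpm, and the number is assumed to be small because of the other screens. This is a cheap safety improvement that should be made. It has no claimed effect on any outcome or analysis.

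**What to change.** In section 2.9, replace the upper heart-rate limit with a resting limit well below 150 bpm, confirmed by repeat readings in the way already used for blood pressure. Possible wording: *resting heart rate above 100 bpm on at least two of three screening readings, each separated by 15 minutes or more*. The value of 100 bpm is an assumption for the sponsor's clinicians to confirm.

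Keep > 150 bpm only as the drug-visit limit in section 2.7. The lower limit of 50 bpm and the bradycardia exemption can stay as they are; this change does not depend on them.

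The cost is one line of text and possibly a few ineligible volunteers. No new procedure is needed, because vital signs and an ECG are already taken at screening and the repeat heart rates can be read with the repeat blood pressures.

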## **2.10 Recruitment and Study Cohort**

Healthy volunteers who report  $\geq 2$  uses of MDMA when they were 18 years or older, recruited to attain 4 sessions of data during functional brain imaging. A total of 40 participants will be recruited, equal

numbers of males and females will be recruited. Participants will be recruited through Facebook Ads using IRB-approved material. Individuals who express interest in the study will be directed to an online screening survey in REDCap. Completed screening surveys will be reviewed by research coordinators trained on the study protocol. Surveys will collect information about demographics, psychiatric diagnoses, substance use, and MRI compatibility. Individuals that are eligible by the criteria included in the screening survey will be contacted by a research coordinator to schedule a phone call. On this phone call, research coordinators will give the individuals additional information about the study and collect additional demographic information. Eligible individuals at this point will be consented by a research coordinator and will schedule an in-person screening visit at a research clinic to fully determine eligibility. The following procedures and assessments will be performed at the screening visit: ECG, physical examination, blood draw, vital signs, weight, urine drug test, pregnancy test (if applicable), Hamilton Anxiety Rating Scale (HAM-A), Hamilton Depression Rating Scale (HAM-D), the Mini International Neuropsychiatric Interview (MINI).

## **2.11 Data collection and management**

### *2.11.1 Plans for assessment and collection of outcomes*

Outcomes for the study will be measured via functional neuroimaging data, self-report questionnaires, and behavioral measures. Neuroimaging data will be collected at baseline and each of the drug visits. Self-report questionnaires will be collected at baseline, each of three drug visits, and at 1-week, and 1-month follow ups. Behavioral measures will be collected at baseline and each of three drug visits. Self-report questionnaires will be collected via REDCap. The only exceptions to this method of administration are the Visual Analog Scale (VAS), the Brief Psychiatric Rating Scale (BPRS), and the Clinician-Administered Dissociative States Scale (CADSS), which will be administered verbally by a trained clinician (BPRS and CADSS) or research coordinator (VAS). Collected measures and their descriptions are included below.

### *2.11.2 Functional Neuroimaging Data*

#### **2.11.2.1 Baseline and Drug Visit scans**

**Resting State:** Participants are instructed to stare at a white cross on a black background. During this time, their eyes will be monitored using an eye-tracker by the study coordinator to ensure that the participant is not asleep. Two separate 5-minute and 12-second runs of resting state data will be acquired, one with a posterior-anterior phase encoding direction and the other with a posterior-anterior direction.

**Monetary Incentive Delay (MID):** Participants watch the screen and see a cue in the form of a circle or square, either of which can be empty or dashed, wait a delay of a varied amount of time, and then seen the target (a white triangle), which they are instructed to respond to with a button press as quickly as possible. The participant is instructed to attempt to press a button while the target is on the screen to

either win money or avoid losing money. A feedback slide is presented after each trial to inform the participant whether they are successful on that trial, and the resulting gain or loss of money. The task is ten minutes long:  $2(\text{valence}) \times 2(\text{magnitude}) = 4 \text{ conditions} \times 12 \text{ trials/condition} \times 12 \text{ sec avg/trial (incl./4 sec avg interval)}$ . This task is meant to elicit neural responses to monetary gain (non-social reward), monetary loss (punishment), and no monetary outcome (control) in striatal and medial forebrain circuitry.

**Facial Expressions of Emotion Task (FEET, conscious and nonconscious):** Participants are presented with two 5-minute and 8-second runs of 3D evoked facial expression stimuli in pseudorandom order – one consciously perceived and one nonconsciously perceived. Each run consists of five repeated blocks of eight stimuli per block, for sad, threat evoked by fear, threat evoked by anger, and happy, relative to the neutral block. Participants are instructed to actively attend to answer post-scan questions about these faces, and we control for active attention by monitoring alertness with an eye tracking system. In the conscious run, stimuli are presented for 500ms with a 750ms interstimulus interval. In the nonconscious run, the same stimuli are presented using a backward-masking design to prevent awareness: each face is shown for 16.7ms, immediately followed by a neutral face mask for 150.3ms, with a 1083ms interstimulus interval to match that of the conscious condition. To control for perceptual priming from the difference in fear-neutral versus neutral-neutral pairs, the neutral faces are spatially offset by one degree in random directions.

**Go-NoGo:** Participants are presented with 240 trials in pseudorandom order over a 5-minute and 8-second run, consisting of 180 'Go' trials and 60 'NoGo' trials. On 'Go' trials, the word "press" is displayed in green, and participants are instructed to respond as quickly as possible. On 'NoGo' trials, the word "press" appears in red, and participants are instructed to withhold their response. Each stimulus is presented for 500ms, followed by a 750ms interstimulus interval.

